### **7.3 Patients who did not receive follow-up visits/contacts**

#### **7.3.1 Premature discontinuation before drug intake**

**In case a participant fulfils all selection criteria, he/she is enrolled in the study and is attributed an enrolment number/participant ID number. If for any reason, the participant cannot be given the study drug and must discontinue participation in the study, the reasons for this will be collected by the CHA or HF staff.**

**These particular subjects will not be part of the safety and efficacy analysis. Additional subjects will need to be recruited in the study in order to make up for the total of 10,000 (9,000 and 1,000) subjects needed for analysis.**

#### **7.3.2 Premature treatment discontinuation**

The reasons of any premature treatment discontinuation will be collected by the CHA or HF staff during his/her visits/contacts and in case the reason to stop the treatment is the occurrence of an adverse event, this will be described on the specific section of the patient chart and treated depending on its category (see section 8).

#### **7.3.3 Patient lost to follow-up**

The study staff will take all appropriate measures to perform each patient's follow-up visits/contacts. However, some patients might be lost to follow up. This information will be recorded in the patient's chart.

A Patient can be considered as lost to follow up if the patient cannot be contacted either by

phone or home visit on scheduled Day (Day 5±2).

In the subset of 1000 patients, a patient can be considered as lost to follow-up if the patient does not present on Day 7 visit and cannot be reached on phone or home visit.

#### **7.4 Thick blood smear logistics**

All thick blood smear slides will be stained and stored for independent confirmation of presence or absence of malaria parasites. They will be examined in the laboratory by qualified personnel and according to the laboratory's Standard Operating Procedures. The results will be transferred for data entry in the form of listings. The blood slides will be performed on Day 1 for all the participants..

#### **7.5 ECG Recording**

In the subset of **about 1,000** patients, electrocardiograms for safety purpose will be performed using the internationally recognized 12 leads with a ELI 150 Cardiograph®. Printouts of each ECG will be individually identified with the subject initial and the subject number, the date and the time of recording, initials of the technician/nurse, initials of the HA; at least 5 complexes for each lead. The corresponding source data will consist of the Cardiograph paper printouts.

The ECGs will be read and analyzed by the study doctor for safety purpose. ECGs will be also read by a central cardiac laboratory and used for the assessment of the possible impact of Eurartesim® on cardiac activity.

The following parameters will be obtained at each time point following the manual reading: RR (ms), HR (bpm), PR (ms), QRS (ms), QT (ms).

For each patient and at specific time point, the triplicate values will be averaged in order to obtain one single value per subject and time point. From the averaged parameter values the following corrected QT interval will be derived:

$$- \text{Fridericia's correction: } QT_{cF}(\text{ms}) = \frac{QT(\text{ms})}{RR(\text{s})^{1/3}}$$

*Note: for the calculation RR is converted in second (RR (ms)/1,000).*

#### **7.6 Vital signs and Physical examination**

Vitals signs include body temperature, weight, pulse rate and blood pressure. Blood pressure and pulse rate will be measured after the patient has rested for 3 min. The physical examination include general appearance, skin, head and neck, eyes, ears, nose, throat, lymph node palpation, lungs, heart, chest, abdomen, neurological function.

#### **7.7 PK sampling**

**About two (2) mL of venous** whole blood samples will be collected from all of the 1,000 subset patients (using direct venipuncture) into 5 mL tubes containing lithium heparin **or EDTA depending on site specific procedures. This will be done at every PK time point**

**making up for a total amount of 8mL to be taken from each participant in this subgroup over the entire study period.**

Each sample will **be** promptly centrifuged and then plasma will be stored at approximately – 75 ± 6°C until shipment to the analytical facilities. All details regarding blood and plasma preparations will be provided in a separate manual of operations.

Concentrations of PQ will be measured in plasma samples. Full details of the methodology will be presented in the bioanalytical protocols.

## **8. SUBJECT SAFETY**

### **8.1 Training**

Before the start of the study, the following training programmes will be completed:

The health facility study staff will be trained on the technique of thick blood smear preparation and staining according to the local Standard Operating procedure and on the recording of ECG data.

The medical staff of the HDSS centres as well as the CHA and the health care provider (HCP) will be trained on the tolerability profile of Eurartesim®, on pharmacovigilance procedures (adverse events recording, adverse events management...) and on study specific other procedures (registry maintenance, non-directional/open patient questioning, filling data sheets) and tools.

The referral hospital staff will be trained on how to recognize and record data of patients who have been referred to them who are taking part in this study. The medical staff of the referral hospitals will be trained on the tolerability profile of Eurartesim®, on pharmacovigilance procedures (adverse events recording, adverse events management...) and on study specific other procedures (registry maintenance, non-directional/open patient questioning, filling data sheets) and tools.

### **8.2 Monitoring of adverse events**

Patient charts (completely filled in with the contact visit at Day 5 (±2 days) or visit Day 7 in the subset of 1,000 patients, and with any AE recording reported in the 28 days after the start of the treatment) will be transferred in triplicate to the Principal Investigator (PI) of the HDSS, every six weeks. Chart review meetings shall be organised regularly, during which the PI, his/her team and the people responsible for the pharmacovigilance in the country participating in the study shall review AEs data (intensity, causality, date of event manifestation in relation to the start of treatment and the initial parasite species identified on the patient). They will determine the causal relationship between any of the recorded adverse event and the medicinal product. This relationship shall be recorded on the patient chart. The notification of the occurrence of serious adverse events, severe adverse events and adverse

events of special interest (which follow a specific process upstream), shall be transmitted to the Local Pharmacovigilance Monitoring Committee every three months for identification of a possible signal.

### **8.3 Definition of Adverse Event and Serious Adverse Event**

An **Adverse Event** (AE) is a sign, symptom, syndrome, disease or biological anomaly suffered by a patient or a subject participating in a clinical study and receiving a medicinal product. This term does not imply a causal relationship with the concerned treatment. Clinical signs typical of an acute malaria episode will not be considered AEs unless the healthcare personnel considers these events as exceptional due to their evolution, their seriousness, or another factor related to these events.

A **Serious Adverse Event** (SAE) is an adverse event which:

- causes death or
- is life-threatening or
- necessitates hospitalisation or prolongs hospitalisation or
- results in invalidity or long-term or significant disability or
- is a congenital defect or malformation or
- is another medically important event.

A decision on medical and scientific grounds is required to assess whether an immediate notification of an event is warranted in other situations, such as medically important events which are not life-threatening, fatal or cause hospitalization, but could endanger the patient or could rendered necessary an intervention to prevent one of the above conditions to develop.

*Remark:* Examples of such events are intensive care in the emergency room or at home to treat a bronchospasm; a haematological dyscrasia; convulsions or an asymptomatic increase ALT ( $\geq 10 \times \text{ULN}$ ) not causing hospitalisation, or the development of drug addiction or abuse.

### **8.4 Obligation of AE notification**

#### ***Adverse Events***

The AEs, regardless of their seriousness and causal relationship to the study drug, arising between the signature of the informed consent form and the last study visit (as per the protocol), must all be recorded on the patient chart (AE recording section). When possible, the symptoms must be regrouped within a single syndrome or diagnosis. The healthcare personnel shall have to specify the date of manifestation of the event, its intensity, final evolution, the measures taken and the treatment undertaken (if any).

#### ***Serious Adverse Events***

In case of SAEs, the healthcare personnel must immediately contact the site PI / Investigator for validation of the seriousness and determination of the causality. Subsequently, the procedure described below must be followed:

- SEND (within 24 hours and fax or pdf scanned documents) the signed and dated copy of the “**Serious** Adverse Event form” and the form “SAE complementary information” to INDEPTH-Network secretariat ([contact]), Study Monitor ([contact]) and the Corporate Safety dept, Sigma-Tau via fax ([name]) or e-mail ([contact]).
- CALL immediately (the same day) the physician of the Sponsor ([contact]) responsible for safety in case of death or life-threatening events.
- CALL the local responsible person for pharmacovigilance of the project.
- The follow-up of each fatal or life-threatening AE must be provided to the Physician of the Sponsor (INDEPTH-Network), the local person responsible for the pharmacovigilance of the project and the Corporate Safety dept – Sigma-Tau within the same timeline as the initial report (within 24 hours and preferably by e-mail/fax).
- ATTACH to the chart the photocopy of all available results and examinations which were undertaken (and their date). Analysis results must be accompanied by the laboratory normal ranges. Special consideration shall be taken to ensure patient anonymity, and to the correct completion of the patient’s study specific identifier in the copies of the source documents provided to the sponsor.

#### ***Follow-up of SAE***

The healthcare personnel must take all appropriate measures to protect the safety of the patients. Personnel must ensure to document follow-up of the evolution of each adverse event (clinical, biological or other) until resolution or until the stabilization of the patient’s status.

All new relevant information concerning the initial SAE shall be recorded on a form “SAE follow-up form” by the nursing staff of the health centre, and shall be validated by the PI / co-PI who shall transfer the form to the to the Physician of the Sponsor (INDEPTH-Network), **the study monitor**, the local person responsible for the pharmacovigilance of the project and the Corporate Safety department – Sigma-Tau.

In case of a serious adverse event, the patient must be followed until complete healing and normalization of all analysis results, or until chronicity of the patient’s status. This can imply that the follow-up of the patient must continue beyond the period of follow-up per protocol, and that additional investigations could be requested by the sponsor.

#### **8.5 Adverse event of special interest**

An adverse event of special interest (AESI) is an adverse event for which on-going monitoring is appropriate within the context of the study. These events necessitate complementary examinations in order to characterize and understand them.

AESIs in this study can be related to:

- Cardio-toxicity i.e. prolonged QT
- Neurotoxicity/seizures

- Cutaneous reactions/phototoxicity

The study team, as well as the relevant referral facilities, should be trained to take particular notice of symptoms/signs suggestive of the AESIs in this study:

-clinical signs of possible cardio-toxicity/prolonged QT such as:

- Palpitations
- Seizures
- Pounding/pain in the chest area
- Fainting/Syncope.

- clinical signs of possible neurotoxicity/seizures such as:

- Seizures
- Dizziness
- Pins and needles sensations
- Visions disturbance
- Difficulties coordination
- Tinnitus

-clinical signs of possible cutaneous reactions/phototoxicity such as:

- Urticaria
- angioedema
- Skin lesions
- Itching pruritus
- Discoloration
- Dermatitis

In all these cases, patients shall be directed to the health facility for evaluation and recording of all relevant information. If an AESI is confirmed, the PI / investigators should be contacted.

In case of an AESI confirmed by the PI / investigators, the sponsor and the Corporate Safety department of Sigma-Tau shall be informed within 24 hours, even if the event does not satisfy any condition of seriousness. **In this last case,** notification will occur through the use of an ad hoc AESI form.

In the case of clinical signs of possible cardio-toxicity, an ECG will be performed as soon as the patient arrives at the health facility to look for the following modifications;

- QTcF >500ms
- Increase of QTcF from baseline >60 ms
- T wave liability, or T wave morphologic changes during therapy

The patient will be asked about the time elapsed from Eurartesim® administration and meal.

The study team should be aware of the fact that, although drug-induced prolongation of the QTc interval is usually asymptomatic, signs of the following clinical events could be potentially associated with a QTc prolongation:

- Torsade de pointes
- Sudden death
- Ventricular tachycardia
- Ventricular fibrillation and flutter
- Syncope
- Seizure.

### **8.6 Pregnancy**

In case of pregnancy, the anti-malarial treatment shall be the one recommended by the NMCP. The patient will not be included in the study.

Female patients will be encouraged to communicate to the CHA if they will be pregnant within a period of two months after the start of the Eurartesim® treatment.

The evolution of the pregnancy will be monitored with visits at 3, 6, 9 months and after the delivery. Information on the drugs taken during the pregnancy as well as AEs/SAEs and the health status of the newborn/s will be collected; thereafter the newborn/s will be followed at 6 and 14 weeks.

### **8.7 Sponsor obligations**

Throughout the study, the sponsor shall report expeditiously all unexpected SAEs which are reasonably related to the study drug to the local responsible person for pharmacovigilance, to the Ethics Committee in accordance with the procedure, and to the investigators. The pharmacovigilance person will submit the reported events to the competent authorities in accordance with local regulations.

The sponsor can also report expeditiously all expected SAEs which are reasonably related to the study drug, to the local responsible person for pharmacovigilance. The latter will submit the reported events to the competent authorities in accordance with local regulations. Each AE not listed as being an expected event in the SmPC and in this protocol shall be considered to be unexpected.

## **9. STATISTICAL METHODS**

The statistical analyses will be performed by INESS using the software package STATA®.

A detailed statistical analysis plan will be generated within three months of study beginning. This plan may be revised during the course of the study in order to take into account the protocol amendments, if any, and to address unexpected problems encountered during the conduct of the study, which could affect the planned analyses. A final statistical analysis plan shall be produced before the database lock.

### **9.1 Analysis of data at study entry**

A descriptive analysis of all data recorded at study entry will be carried-out in order to characterize the population under study.

### **9.2 Analysis in the whole sample**

#### **Analysis in the whole sample and in the Subset population**

The statistical analysis will be mainly descriptive. The estimates of the incidence of adverse events will be based on crude rates. All estimates will be complemented with appropriate 95% confidence intervals.

The adverse events shall be regularly coded using MedDRA before database lock.

All SAEs and AESIs will be reviewed centrally by an independent safety monitoring panel.

Incidences will be computed on the following classes of AEs, overall and by SOC/PT:

- All AEs
- Serious AEs
- Serious AEs related to study treatment
- AEs of special interest (AESIs)
- AEs which caused early discontinuation of Eurartesim®
- AEs related to Eurartesim® treatment

Specific analyses will be carried-out on the AESIs. Correlation analyses will be carried-out in order to verify if their occurrence is more frequent with the previous/concomitant use of other drugs (specific classes to be determined in the statistical analysis plan), including antimalarials, in presence of co-morbidity (specific classes to be determined in the statistical analysis plan), or in presence of parasitaemia.

Compliance will be computed in the whole population and in the subset of **about 1,000** patients, calculating for each patient the ratio between the number of tablets taken and the number of tablets that the patient should have taken. Two groups of patients shall be described: compliant = 100% treatment compliance and non compliant = other cases. The safety profile of compliant vs non-compliant patients will be compared.

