|                                        | 
concentration at Day 1 (before drug administration), twice at Day 3 (before and 3-4 after the last drug administration) as well as on Day 7.
 
 
• The relationship between the occurrence of adverse events and the administration of concomitant medications will be evaluated in the subset of 1,000 patients.
 
• Compliance to study treatment will be assessed on the whole population by asking to the patient if he/she adhered with the treatment prescription on the <math>5 \pm 2</math> days contact. In the 1,000 patient subset, compliance will be evaluated counting the number of tablets dispensed but not taken.
 
                                                                                                                                                                                                                                                                                                                                                                                                                                                                                                                                                                                                                                                                                                                                                                                                                                                                                                                                                                                                                                                                                                               |

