### 7.2.2 Examination and data collection at inclusion

In case the patient meets the protocol selection criteria and agrees to participate in the study, the following procedures will be followed:

- An informed consent form will have to be signed and will be filed with the registry.
- The HF will assign a patient ID number to the patient, visit the patient as usual and record the following data:
  - On the patient chart: last name, first name, full address (village/neighbourhood), registration number and patient ID number.
  - On the rest of patient chart: the other information collected during this visit, i.e.:
    - Demographic data of the patient: patient ID number, initials, age, sex, weight and body temperature.
    - Intake of anti-malarial drugs during the 4 weeks before inclusion.
    - Intake of any other treatment including traditional treatments, during the 2 weeks before inclusion.
    - Concomitant treatments and treatments prescribed when visiting the centre.
    - Malaria and associated disease symptoms will also be reported.
    - Confirmation that a thick blood smear identified by the patient's ID number and the date of blood withdrawal has been taken and prepared for later reading.
    - Confirmation that a blood sample for haematology, blood chemistry and PK (where foreseen) has been drawn in the subset of patients more closely evaluated; and that in the same subgroup a triplicate ECG has been recorded. Results of the ECGs local readings and laboratory examinations will be reported as soon as possible on the chart (copy of the results have to be stored at site).
    - Eurartesim® treatment administration time. Dosage will be defined according to the weight of the patient. The patient will be instructed to take the medication with water, between meals as described in section 5.3. In all the 10,000 patients the first dose of the study drug will be directly administered at the facility and time of administration and time of last food consumption will be annotated.

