### 7.2.3 Follow-up visits/contacts and clinical tolerability follow-up questionnaire

At Day 5 ( $\pm 2$  days) (after administration of the last Eurartesim® dose) following the inclusion date, the community health agent (CHA) will contact the patient at home. A further visit at the patient's home will be scheduled by the community health agent in all the cases in which the information collected during the telephone contact should be considered incomplete or unreliable ones.

He/she will then fill-in the second part of the chart (in triplicate) and report:

- His/her own 4 digit identification number (first two digits are the number of the health centre he/she is attached followed by a 2 digit number which will be assigned to him/her when the study starts).
- Date of the visit/contact.
- Clinical condition (recovered status or continuation of the illnesses).
- Compliance with the prescribed Eurartesim® treatment and in case, number of tablets of Eurartesim® not taken; an explanation of the reason why the treatment was not followed should be provided.
- Description of the symptoms experienced by the patient in case of a positive answer to the question: *“Have you noticed any unusual event/symptom since your last visit at the centre?”* Collect date of first manifestation of this/these event(s), symptom(s), intensity, treatment dis-/continuation, and evolution, in the specific section of the patient chart dedicated to the collection of Adverse Events.
- Current treatments, if taken.

In case, during his/her contact, the CHA assess that an occurred event is serious and/or severe, or detects an adverse event of special interest (see section 8.5), he/she should contact the HA and transfer the patient to the health facility in order to be examined. If necessary in the opinion of the HA, he/she should contact the investigators so that they can visit the patient and exactly define the status of the event and the causality. If the adverse event belongs to the cardiovascular category, an ECG will be performed. In addition, a thick blood smear will be prepared (for future analysis). In that event, a specific adverse event report form will be completed by the HA or the investigators.

The patient will receive first care treatment. In case any other treatment is prescribed by a HA staff or the study doctor, it will be reported on the patient chart.

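### The two-group compliance rule has no class for unknown compliance, so read literally it counts dosed main-group patients lost at the Day 5 contact as non-compliant

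*Protocol*

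**What the plan says.** Section 9.2 (under the sub-heading for the whole sample and the subset) measures compliance by "calculating for each patient the ratio between the number of tablets taken and the number of tablets that the patient should have taken". It then sets two groups: "compliant = 100% treatment compliance and non compliant = other cases". The use made of them is stated: "The safety profile of compliant vs non-compliant patients will be compared". On the estimator, the same section says: "The estimates of the incidence of adverse events will be based on crude rates". The Summary repeats the compliance rule.

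The inputs to the rule are set elsewhere in the protocol:

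- **Source of tablet data.** The Summary assesses compliance in the whole population "by asking to the patient if he/she adhered with the treatment prescription on the" Day 5 (±2) contact. Section 7.2.3 lists "Compliance with the prescribed Eurartesim" treatment, and the number of tablets not taken, among the items recorded then. The open question about AEs is asked at the same contact.
- **Loss to follow-up.** Section 7.3.3: "A Patient can be considered as lost to follow up if the patient cannot be contacted either by" phone or home visit on the scheduled day. In the nested subset, loss is tied to the Day 7 visit instead.
- **Dosing.** Section 7.2.2: "In all the 10,000 patients the first dose of the study drug will be directly administered at the facility".
- **Exclusions.** Section 7.3.1 removes from the safety analysis only enrolled patients who were never given the drug.

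**The concern.** The second group is a residual: it takes whatever is not 100% compliance. A main-group patient who takes the supervised first dose and then cannot be reached has an unknown tablet count, is not excluded by section 7.3.1, and is not shown to be 100% compliant. Taken at its word, the rule files that patient as non-compliant.

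This does more than add noise, because one missed contact removes both the tablet count and the solicited AE report. With crude rates, such patients add to the denominator of one group only and bring few or no solicited events. The comparison could then suggest that patients who did not finish treatment had fewer AEs than those who did, when part or all of the gap reflects who was asked.

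**Working it through.** The protocol gives no figure for this comparison, so there is none to reproduce. The check has two parts.

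**1. Where a lost main-group patient goes**

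- First dose given at the facility (7.2.2), so not removed by 7.3.1.
- Not reached by phone or home visit at Day 5 (±2), so lost under 7.3.3.
- No tablet count from 7.2.3, so the ratio in 9.2 cannot be computed.
- Not shown to be 100% compliant, so by the literal rule an other case.

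The nested subset is largely spared. The second dose is preferably given at the site, or at home by a trained community health agent with a diary (5.3). The third dose is observed on Day 3 (7.1, 7.2.3), and compliance is recorded at that visit (7.2.3). A nested patient can miss Day 7, count as lost, and still have known compliance.

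**2. Effect on the all-AE rate**

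The loss, non-compliance and AE rates are assumptions, because the protocol states none of them. Let L be the share lost, q the non-compliance among contacted patients, r the true AE rate (set at 20% in everyone) and c the fraction of lost patients' AEs still captured by passive routes. Then

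apparent rate in the non-compliant group = r × [(1−L)q + Lc] / [(1−L)q + L].

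Example with L = 3%, q = 5%, c = 0: (1−L)q = 0.97 × 0.05 = 0.0485, and 0.0485 / (0.0485 + 0.03) = 0.618, so the rate reads 0.20 × 0.618 = 12.4%. With c = 0.25: (0.0485 + 0.0075) / 0.0785 = 0.713, or 14.3%.

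Counts below use the main group of 9,000 given in section 7.3.1. The ratios do not depend on that number.

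| L | q | c | True non-compliers contacted | Lost | Lost as share of group | Apparent rate | Apparent/true |
|---|---|---|---|---|---|---|---|
| 1% | 20% | 0 | 1,782 | 90 | 4.8% | 19.0% | 0.95 |
| 1% | 5% | 0 | 446 | 90 | 16.8% | 16.6% | 0.83 |
| 3% | 10% | 0 | 873 | 270 | 23.6% | 15.3% | 0.76 |
| 3% | 5% | 0 | 436 | 270 | 38.2% | 12.4% | 0.62 |
| 3% | 5% | 0.25 | 436 | 270 | 38.2% | 14.3% | 0.71 |
| 5% | 5% | 0 | 428 | 450 | 51.3% | 9.7% | 0.49 |

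The compliant group stays at 20% throughout. With c = 1 the ratio is 1.00 in every row. It is also 1.00 if lost patients are kept out of both groups.

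**SAEs.** Take L = 3%, q = 5% and an SAE rate of 0.5% in contacted non-compliers. If none of the lost patients' SAEs are captured, the group reads 0.0485 × 0.005 / 0.0785 = 0.31%. If hospital data show a 2% SAE rate in lost patients, it reads (0.0485 × 0.005 + 0.03 × 0.02) / 0.0785 = 1.07%. The sign is not fixed.

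**The case against.** The strongest reply is that the rule should be read with the sentence before it: a ratio is computed for each patient, so the residual group means a computed ratio other than 100%, and a patient without a ratio is unclassified. That reading is possible, but the text does not state it, and the residual wording points the other way.

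A second reply is that missing derived variables belong in the statistical analysis plan, which may exist and is not shown. Section 9.2 does defer some things to that plan, namely the drug classes and co-morbidity classes. It does not defer the compliance groups; it defines them itself. So this is a rule the protocol states, not a silence left for later.

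Three further points stand and limit the finding.

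- A reader might infer that lost patients have no AE data at all. They do have some: AEs are recorded at Day 1 (flow chart), patients are told to report events up to Day 28, and regional-hospital data on participants are collected (5.1, 7.2.3). What is missing is the solicited Day 5 report.
- A reader might infer that the non-compliant group must be small and the bias large. The protocol supports neither. Doses 2 and 3 are unsupervised in the main group, so non-compliance could be common, and loss requires both phone and home visit to fail, so it could be rare.
- The comparison is not a listed objective, sits in a mainly descriptive analysis, and has no stated test or decision rule.

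**Conclusion.** The point holds in a limited form. As written, the rule puts dosed main-group patients lost at Day 5 (±2) into the non-compliant group and distorts the planned compliant versus non-compliant comparison. If true AE rates are alike, the all-AE rate in that group is biased downward whenever lost patients' AEs are captured less completely than those of contacted patients. A claim that every AE class is biased downward would go too far, since SAEs found through hospitals or spontaneous reports can move the rate up.

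The size cannot be computed from the protocol. Under the assumed 20% AE rate, the ratio runs from about 0.95 (1% loss, 20% non-compliance) to 0.49 (5% loss, 5% non-compliance), both with no passive capture, so the effect may be negligible or may halve the apparent rate.

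It would also be wrong to infer that the primary result is affected through this route: the whole-sample incidences do not use the compliance groups. It is a secondary comparison, but one that could yield a misleading safety statement and is easily repaired.

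**What to change.** In section 9.2 and the Summary:

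1. Define non-compliant as a known tablet ratio other than 100%.
2. Add a third class, compliance unknown, meaning no recorded tablet information from the Day 5 (±2) contact in the main group, or from the Day 3 and Day 7 visits in the nested group. A missed Day 7 visit alone should not place a nested patient here if compliance was recorded on Day 3.
3. Restrict the safety comparison to patients with a known ratio.
4. Report the number of patients with unknown compliance, and their AEs, by site.

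The cost is a sentence or two of wording. No new data are needed, because tablet counts and loss to follow-up are already recorded in the patient chart. The downside is that the comparison then omits patients with unknown compliance, which is why they should be shown separately.
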